#### Distress Screening

The single item Brief Distress Thermometer (BDT) will be used to screen for global psychological distress [13]. This scale has good sensitivity and specificity when used with a cut off point of ≥ 4 [14].

#### Psychological Distress

The Brief Symptom Inventory – 18 (BSI-18) will assess psychological distress through three subscales of anxiety, depression, and somatisation [35].

#### Cancer Specific Distress

The Impact of Events Scale (IES: [36,37]) will be used to assess cancer specific distress. The IES has two subscales that measure the extent to which participants are experiencing intrusive thoughts about cancer and avoiding thinking about cancer [38].

#### Unmet Psychological Supportive Care Needs

The Supportive Care Needs Survey Short Form 34 (SCNS-SF34) will assess cancer patients' need for help over the last month across 5 domains: psychological, health systems and information, patient care and support, physical and daily living, and sexuality needs [39,40]. The Supportive Care Needs Survey for Partners and Caregivers (SCNS-P&C45) will assess carers' need for help over the last month.

#### Positive Adjustment

Positive adjustment will be measured with a 21-item Posttraumatic Growth Inventory (PTGI) assessing perceived positive life changes occurring after a diagnosis of cancer [41]. Domains assessed include strengthened relationships with others, appreciation of life, personal strength, new priorities, spiritual/religious growth.

#### Quality of Life

Health related quality of life will be measured with the Assessment of Quality of Life – 2 (AQoL-2), which is a more recent version of the original 15-item AQol. The AQoL-2 is a 20-item scale assessing quality of life on six dimensions; including independent living, social, mental health, coping, pain, and sensory perception [42]. The AQoL will also be used to assess the cost-effectiveness of the intervention options. AQoL utility data analysis will be used to estimate Quality-adjusted life years (QALYs).

### Statistical Analyses

The study is a multivariate, two condition randomized controlled trial with repeated measures across time. The analytic approach will be a multilevel model (MLM) in which measurement occasions (level 1) are nested within persons (level 2) and in which state/program differences are represented as a fixed effect at level 2 whose interaction with time represents differential adjustment and distress trajectories for the two groups. A key advantage of this approach is flexibility in dealing with missing data owing either to random or non-random attrition. Further, subgroups of patients and carers who respond differentially to the program will be identified using growth mixture modelling that is a related longitudinal procedure that identifies cases with similar distress and adjustment trajectories across time [43]. Jo's [44] results suggest that the proposed sample size will be sufficient to examine subgroups of responders.

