### Intervention

The 'self help' self management materials will consist of an initial single 30-minute telephone support and education session with a nurse counsellor who will provide feedback to the participant about his/her levels of distress and instruction in evidence based strategies to improve adjustment. A self management manual will be developed purposefully for this study that will include self help in mood/stress management skills; problem solving approaches to cancer-related concerns; patient education about a healthy lifestyle to promote wellness and optimise quality of life; strategies for mobilising personal and community support networks to reduce isolation and seek sustainable social support. For the individualised cognitive behavioural intervention (therapist delivered), five weekly one-hour sessions of tele-based counselling from a clinical psychologist will be delivered that include psychoeducation, skills in stress reduction, problem-solving, cognitive challenging and enhancing relationship support. Cognitive behavioural approaches are well established with regards to their clinical efficacy for anxiety and depression in cancer and individualised approaches are more effective than groups [29]. The individualised counselling sessions will follow principles of cognitive-behavioural therapy and will utilise an adult learning approach in which participants self-select goals to focus on during the intervention. Content will include assigned behavioural homework that will be supported by work and tip sheets. Components that target challenges associated with cancer treatments (e.g., pain, sleep disturbance, fatigue) will be additionally selected if relevant. Minutes of counselling time will be recorded for inclusion in analyses for both arms.

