### Participants

Study inclusion criteria will be that the patient/carer participants must: (1) be a cancer patient or carer ≥ 18 years of age who has called the Cancer Helpline for information or support (2) have a score of 4 or more on the Brief Distress Thermometer at the time of the Helpline contact (3) be able to read and speak English (4) have no previous history of head injury, dementia or psychiatric illness.

Callers who meet the selection criteria will be offered entry into the study by the Helpline operator at the time of the call; and once verbal permission to be contacted is obtained will be posted written consent and information forms. To minimise the period of time between calling the Helpline and randomisation into a support arm of the study, verbal consent to take part in the study will be obtained by project staff and audio taped prior to written consent. Baseline assessment will be conducted via telephone interview to prevent potential delays in receiving support. Participants will then be randomly allocated to receive either self management or the five session cognitive behavioural intervention. In all, 140 patients and 140 carers per condition will be recruited (allowing for a total of 280 people per treatment arm; 560 participants in total). On the basis of simulation work conducted by Raudenbush and Xiao-Feng [33], the present study, with 4 measurement periods and a total N of 560 will have power of at least .90 to detect a moderate longitudinal effect size. This sample size will allow for identification and investigation of subgroups of patients and carers (high vs. low/borderline distress) on the basis of their response to psychological intervention.

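### The two-level model has no psychologist term for the CBT arm, so if outcomes vary by psychologist the standard error of the arm-by-time effect is too small

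*Protocol article*

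**What the plan says.** The Statistical Analyses section sets out the hierarchy level by level: "a multilevel model (MLM) in which measurement occasions (level 1) are nested within persons (level 2"). It places the arm at the upper of these levels: "state/program differences are represented as a fixed effect at level 2 whose interaction with time represents differential adjustment". No level or term represents the person who delivers the treatment.

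The Intervention section describes two very different provider contacts. In the CBT arm, "five weekly one-hour sessions of tele-based counselling from a clinical psychologist will be delivered". In the comparator, contact is "an initial single 30-minute telephone support and education session with a nurse counsellor", backed by a self-management manual.

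The Participants section fixes the numbers: "140 patients and 140 carers per condition will be recruited", "allowing for a total of 280 people per treatment arm; 560 participants in total". It states that the trial "will have power of at least .90 to detect a moderate longitudinal effect size". It mentions neither clustering by provider nor the number of psychologists. Under Study Integrity, randomisation is stratified by patient/carer status and state only. Therapy is to be manualised, and intervention calls are taped and reviewed for adherence.

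**The concern.** People treated by the same psychologist share that psychologist's skill, style and adherence, so their outcomes may be correlated. Psychologists work in the CBT arm only, which makes the trial partially nested: that arm has a source of dependence that the comparator lacks or has in weaker form. A model that stops at persons counts differences between psychologists as if they were averaged over 280 independent people. In fact they are averaged over the number of psychologists.

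The arm contrast then looks more precise than it is. Confidence intervals are too narrow, and the chance of declaring CBT better than minimal contact when it is not rises above the nominal level. This bears on hypothesis 3, the only hypothesis on clinical outcomes that compares the two arms.

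**Working it through.** **Inputs from the article.** 280 people per arm; five one-hour sessions each in the CBT arm; a five-month intake (Study aims and hypotheses); four measurement occasions; stated power of at least .90.

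**Inputs assumed, because the article does not give them.** Two-sided alpha .05; number of psychologists k; therapist intraclass correlation (ICC); 20 client-hours a week per psychologist; a moderate effect taken as a standardised difference of d = 0.5; half of participants high-distress.

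**Step 1: the stated power.** It cannot be reproduced exactly, because the effect size has no number and the variance components are not given. A simple comparison of 280 with 280 has power .900 at d = 0.274, .944 at d = 0.30 and above .999 at d = 0.5. Without clustering, the claim of at least .90 is comfortably met.

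**Step 2: how many psychologists?** 280 × 5 = 1,400 session-hours. Five months of intake plus five weeks to finish is about 26 weeks, and 1,400 / 26 ≈ 54 hours a week. At 20 hours each, 54 / 20 ≈ 2.7, so roughly three psychologists or more. I use 4 to 10 as the main range and show 3 as well.

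**Step 3: effect on the standard error.** With m = 280/k people per psychologist:
- design effect in the CBT arm: DE = 1 + (m − 1) × ICC
- true SE divided by model SE: f = √((DE + 1)/2), since the comparator keeps a design effect of 1
- actual two-sided error: 2 × (1 − Φ(1.96/f))

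| k | m | ICC | DE | f | error |
|---|---|---|---|---|---|
| 10 | 28 | .01 | 1.27 | 1.07 | .066 |
| 10 | 28 | .05 | 2.35 | 1.29 | .130 |
| 4 | 70 | .01 | 1.69 | 1.16 | .091 |
| 4 | 70 | .05 | 4.45 | 1.65 | .235 |
| 3 | 93.3 | .05 | 5.62 | 1.82 | .281 |

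At ICC = 0, f = 1 and the error is .05.

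**Step 4: hypothesis 3.** This covers only participants with high anxiety/depression, so the clusters are smaller. With 140 per arm, m is 14 (k = 10) or 35 (k = 4).
- k = 10, ICC .01: DE = 1.13, f = 1.03, error .058.
- k = 4, ICC .05: DE = 2.70, f = 1.36, error .150.

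**Step 5: check on slopes.** The formula in step 3 is for a single mean, but the plan tests a trajectory difference. A simulation (4,000 replicates, 280 per arm) compared person-level slopes, with psychologist variation in slope in one arm. The ICC was defined on the true slope, and half of the observed slope variance was measurement noise. Rejection was about 5% at ICC 0. At ICC .02 and .05 it was .103 and .183 (k = 3), .077 and .119 (k = 6), and .067 and .091 (k = 10). The direction is the same. The size is smaller than in step 3 because measurement noise halves the ICC of the observed slopes.

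**Step 6: power after correction.** At d = 0.5 with a normal reference, power is √(280/2) × 0.5 / f − 1.96 referred to the normal distribution. For k = 4 and ICC .05 this is 5.916/1.651 − 1.96 = 1.62, so power is about .95; for k = 3 it is .902. A small-sample reference costs more. For k = 4 and ICC .05 the Satterthwaite degrees of freedom are (4.45 + 1)² / (4.45²/3 + 1²/279) ≈ 4.5, and power from the noncentral t distribution is about .79. For k = 10 and ICC .05 the same calculation gives about 18 degrees of freedom and power of about .99.

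**The case against.** **The size is assumed.** The number of psychologists, their caseload and the ICC are not in the article, and manualised therapy with taped calls may push the ICC towards zero. This stands. It makes the size conditional, but it does not change the direction, and adherence monitoring does not put any remaining variation into the standard error.

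**It is a condensed article.** A provider term is often left to the full analysis plan. That would answer a silence. Here the levels of the model are named, and the named hierarchy ends at persons. A further random effect in the full plan is not ruled out, but the model as published does not include one.

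**The comparator also has a provider.** True: a nurse counsellor gives one call. Clustering there is probably weaker after 30 minutes, but it may not be nil, which is why the provider should be recorded in both arms.

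**A stronger reading is tempting for patient-carer pairs.** A reader might infer that a patient and that patient's own carer, if both enrol and are randomised separately, make the standard error too small in the same way. The document does not support this. It does not say that enrolled carers belong to enrolled patients, only that each participant called the Helpline. Even if many pairs enrolled, about half would fall in the same arm and half in opposite arms, so the pair covariance roughly cancels in the arm difference. A simulation of 280 complete pairs with an assumed correlation of .5, separate blocks of 10 and an analysis that ignored pairs gave a type I error of .048. Allocating pairs together and ignoring them gave .111, so joint allocation would create the dependence rather than cure it.

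**Conclusion.** The concern holds conditionally. The stated model omits a source of dependence that the design probably creates in one arm. For any therapist ICC above zero, the standard error of the arm-by-time effect is too small and the error rate exceeds 5%.

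Under 4 to 10 psychologists and ICC .01 to .05, both assumed, the cross-sectional approximation gives an error of about .066 to .235 for the whole-arm comparison. For hypothesis 3 it gives about .058 to .150 if half of participants are high-distress. The whole-arm range should not be quoted for hypothesis 3, and the slope simulation suggests smaller inflation when slopes are measured with noise.

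A reader might also infer that the sample size is inadequate. The documents do not show that: the .90 claim for a moderate effect is not overturned. Taking moderate as d = 0.5, normal-theory power for the whole arms stays above .90 throughout the assumed range. It falls below .90 only with few psychologists, a high ICC and a small-sample reference together. The main damage is to type I error and interval width. With a single psychologist, therapist and arm would be fully confounded and no model could separate them, but the workload makes that unlikely.

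**What to change.** - Record the treating provider for every participant in both arms. Without this identifier the dependence cannot be modelled later.
- In the CBT arm, add a psychologist random effect on change over time, as a therapist-by-time or post-baseline effect in a partially nested model. A random intercept alone is not enough: it would place a therapist effect at baseline, before randomisation and before any psychologist is met, and would add no therapist variance to the arm-by-time contrast.
- Use small-sample degrees of freedom, and report the estimated ICC with the number of psychologists and their caseloads.
- State the assumed ICC and number of psychologists beside the sample size.

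The cost is one identifier and the added variance term. Intervals become wider, more so with few psychologists, and the variance will then be poorly estimated. If the ICC proves close to zero, the estimated standard error changes little, although few degrees of freedom can still widen the interval.

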### Study Integrity

Ethical approval has been obtained from the Griffith University Human research ethics Committee. The study design will be guided by the CONSORT statement [34]. Randomisation to study condition will occur following the completion of baseline assessment. Assessments will be by self-report pen and paper measures and project staff tracking assessments will be blinded to condition. Randomisation will be stratified by patient/carer and state (QLD vs NSW) and will occur in blocks of 10, with each condition randomly generated 5 times within each block to ensure an unpredictable allocation sequence with equal numbers of participants in each group at the completion of each block. This sequence will be undertaken by the project manager and concealed from investigators. Therapy will be manualised and all intervention calls audiotaped and reviewed to monitor treatment adherence. All analyses will be conducted on the basis of intention to treat.

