### Measures

A computer assisted telephone interview will be undertaken for the baseline assessment; subsequent assessments will be administered by mail at 3, 6 and to 12 months after recruitment. A short telephone interview at follow-up time points will also re-assess participants' use of support services. Primary outcomes are anxiety and depression, cancer specific distress and unmet psychological supportive care needs. Secondary outcomes are positive adjustment and overall quality of life.

Background variables will include socio-demographic and disease variables (e.g. cancer site and stage, medical treatments received, use of alternative therapies) and previous (past month) and current use of support services.

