### Economic Analyses

A trial-based economic evaluation will be conducted that integrates the efficacy and quality of life outcomes data with comparative cost data on the intervention options. The various distress indicators and the unmet needs data will be built in incremental cost-effectiveness analysis (CEA), while the quality of life data will be used in cost-utility analysis (CUA) using the Brazier algorithm. The feasibility of adding a modelled economic evaluation (to broaden the target population; lengthen the time horizon beyond that of the trial; and estimate cost offsets) will also be carefully assessed, having regard to trial results and the strength of evidence in the literature to underpin key modelling assumptions.

Costs and outcomes will be assessed from a health sector perspective, but with a focus on 'government as 3^rd ^party funder'. Cost impacts that fall on patients and their carers/families will be reported to the extent they can be assessed from the activity data; but this collection will not be complete. Pathway analysis and patient flowcharts (incorporating decision tree analysis) will be used to clearly identify and cost the activity components for each arm of the trial. Standard discounting will be applied to both costs and outcomes, together with detailed sensitivity testing (using @RISK probabilistic software).

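### The plan credits its multilevel model with dealing with non-random attrition, but the model it describes is valid only if data are missing at random

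*Protocol article*

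**What the plan says.** The Statistical Analyses section of the protocol article plans a two-level model, occasions within persons, with group differences as a fixed effect whose interaction with time carries the comparison. The next sentence reads: "A key advantage of this approach is flexibility in dealing with missing data owing either to random or non-random attrition". The approach referred to is the multilevel model. Growth mixture modelling comes afterwards, for a different purpose: "subgroups of patients and carers who respond differentially to the program will be identified using growth mixture modelling". No model of the drop-out process is described.

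Under Measures, the baseline is a telephone interview, and "subsequent assessments will be administered by mail at 3, 6 and to 12 months after recruitment". The primary outcomes are anxiety and depression, cancer-specific distress, and unmet psychological supportive care needs. Hypothesis 1 (Study aims and hypotheses) concerns improvement from baseline in both arms; hypothesis 3 compares the arms among participants with high anxiety or depression. The only sensitivity testing mentioned is in Economic Analyses and belongs to the economic evaluation.

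**The concern.** A likelihood-based model of repeated measures uses every observed occasion. Its inference is valid when the chance of being missing depends only on data that were observed and are in the model. If a participant fails to return a questionnaire because of distress at that moment, which nobody recorded, the model predicts the missing value from people who did return theirs, and that prediction is off. Correcting for this needs either a model of drop-out or an explicit assumption about how non-returners differ. The plan describes neither, yet tells the reader that the method deals with this kind of loss.

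The setting makes the point more than formal. Everyone enters with elevated distress, outcomes are self-reported, and follow-up is postal for 12 months. The arms also differ in contact (Intervention): five weekly one-hour sessions against one 30-minute call. Distress-related non-return, and a difference in it between arms, are plausible, though the article does not document either. The wrong assurance could make a sensitivity analysis seem unnecessary and lead readers to treat the estimates as robust to a mechanism they are not robust to.

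**Working it through.** **The plan's own figure.** The Participants section says that the study "with 4 measurement periods and a total N of 560 will have power of at least .90 to detect a moderate longitudinal effect size". It gives no alpha, numerical effect size, variance components or attrition rate, so the figure cannot be reproduced strictly. As a plausibility check with two-sided alpha 0.05 (assumed) and 280 per arm, the smallest standardised difference with 90% power is (1.960 + 1.282) × √(2/280) = 0.27. A moderate effect is therefore within reach before attrition. This does not bear on the present point, which concerns bias rather than power.

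**Step 1: simple bias formula.** Bias in the arm difference ≈ m₁δ₁ − m₀δ₀. Here m is the share missing in an arm, and δ is how far its non-returners lie, in SD, from what missing at random predicts. Both are assumed.

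- Alike in both arms (m₁ = m₀, δ₁ = δ₀): 0.
- Departure in one arm only:
  - m = 0.25, δ = 0.3: 0.25 × 0.3 = 0.075 SD
  - m = 0.25, δ = 0.5: 0.25 × 0.5 = 0.125 SD
  - m = 0.30, δ = 0.3: 0.30 × 0.3 = 0.09 SD
  - m = 0.30, δ = 0.5: 0.30 × 0.5 = 0.15 SD

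The range is thus 0 to 0.15 SD when only one arm departs.

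**Step 2: simulation of the planned type of model.** From the article: 280 per arm, and occasions at 0, 3, 6 and 12 months. Assumed: random-intercept variance 0.5, slope variance 0.3, covariance −0.05 and residual variance 0.3, which give a 12-month SD of √(0.5 − 0.10 + 0.3 + 0.3) = 1.0. Also assumed: a true 12-month change of −0.30 in the control arm, and monotone drop-out of 25–31% by 12 months. The model was fitted by generalised least squares with the true covariance, in 1,500 replicates. Under missing at random, drop-out depends on the previous observed score; under missing not at random, on the current score that is lost. Arm difference means extra improvement in the intervention arm.

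| Drop-out | True arm difference | Bias in arm difference | Rejection rate | Control change (true −0.30) | Intervention change (true) |
|---|---|---|---|---|---|
| At random, opposite by arm | 0 | 0.000 | 0.061 | −0.300 | −0.300 (−0.30) |
| At random, opposite by arm | 0.30 | 0.001 | 0.919 | −0.299 | −0.600 (−0.60) |
| Not at random, opposite by arm | 0 | 0.199 | 0.595 | −0.185 | −0.384 (−0.30) |
| Not at random, opposite by arm | 0.30 | 0.185 | 1.000 | −0.184 | −0.669 (−0.60) |
| Not at random, alike in both arms | 0 | 0.000 | 0.053 | −0.384 | −0.384 (−0.30) |
| Not at random, alike in both arms | 0.30 | −0.015 | 0.911 | −0.384 | −0.669 (−0.60) |

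**Step 3: reading the results.**

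- Missing at random: the model does what it should. Bias stays within 0.005, also when drop-out is completely at random.
- Missing not at random, opposite by arm: the two departures add. Under the null, the control change is off by −0.185 + 0.30 = 0.115 and the intervention change by −0.384 + 0.30 = −0.084; the arm difference is off by 0.115 + 0.084 = 0.199. This exceeds the range in step 1 because both arms depart, and it is an extreme case.
- Missing not at random, alike in both arms: the departures nearly cancel between arms, but improvement within each arm is overstated. A true 0.30 appears as 0.384 (by 0.084), and a true 0.60 as 0.669 (by 0.069).

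**The case against.** The strongest defence is that the sentence claims only flexibility, and that non-random may loosely mean attrition related to recorded variables. That would be missing at random, and the claim would be defensible. The reading is possible but strained: the text sets random against non-random without qualification, and nothing limits the second term to observed causes. Even on that reading, the assumption that the analysis rests on is not stated.

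Several stronger readings are tempting, and the documents do not support them.

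- **That informative drop-out would bias the result.** It can, but size and direction depend on the mechanism. If it acts alike in both arms, the arm contrast is nearly untouched. The article gives no attrition rate and no evidence of differential loss.
- **That no check is planned.** Only a condensed article is at hand. A missing-data sensitivity analysis is commonly left to the analysis plan, so its absence here is no fault. The error is the assurance that is stated.
- **That the plan relies on this model to satisfy intention to treat.** Study Integrity says "All analyses will be conducted on the basis of intention to treat", but does not mention missing data or the model, and Statistical Analyses does not mention intention to treat. No text joins the two.
- **That the bias is a known fraction of the target effect, or a known number of standard errors.** The protocol gives no number for a moderate effect, and a single-occasion two-sample standard error is not that of the planned group-by-time effect.

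**Conclusion.** The point holds as an error of statement. The multilevel model as described is valid under missing at random given the observed data in the model. It does not deal with attrition that depends on unobserved outcomes, and neither the growth mixture model nor the economic sensitivity testing is presented as supplying that property.

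For the arm contrast, the possible bias runs from about zero (mechanism alike in both arms) to about 0.15 SD (30% missing and a 0.5 SD departure in one arm only). It is larger only if the arms depart in opposite directions. For hypothesis 1, bias is possible even when the arms behave alike. All these sizes rest on assumed missing shares, departures and variance components; they show what can happen, not what will. The conclusion that the sentence is wrong does not depend on them.

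**What to change.** Replace the sentence with: *The multilevel model is valid if data are missing at random given the observed data in the model.*

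If any claim about non-random attrition is to stay, support it with a pre-specified sensitivity analysis of the primary outcomes: delta-adjusted multiple imputation or a pattern-mixture model. Vary delta separately by arm until the conclusion changes, and report that tipping point. Include the case of equal deltas in both arms, so that the effect on within-arm change is visible. If the statistical analysis plan already contains such an analysis, it is enough to confirm this and refer to it.

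The cost is one corrected sentence and one extra analysis of data already collected. The main model, the sample size and the data collection stay as they are.
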